### Evaluation design

The evaluation assesses the feasibility of implementing the MOUD 2.0 algorithm in primary care clinics through a retrospective chart review of clinical outcomes. Feasibility denotes advancing the algorithm’s objectives—improved adherence and retention—while maintaining patient access to consistent, measurement-based treatment. The algorithm is implemented at the clinic-wide level to preserve fairness between patients and clinicians, per the algorithm goal, as it would be unethical to exclude patients with OUD from treatment in the program. Therefore, structuring the evaluation as a retrospective implementation evaluation is more appropriate than as a randomized clinical trial to ensure full equal access to treatment.

The implementation evaluation will first be conducted at a Philadelphia Integrated Care Clinic (ICC), which is a partnership between Pathways to Housing PA, a housing-first agency and Project HOME Healthcare Services (PHHS), a Federally Qualified Health Center (23, 24). The ICC includes addiction and primary care physicians, psychiatrists, social workers, and support staff. The clinic serves a steady population of patients with OUD for ongoing primary care and MOUD.

The evaluation is an initial observational evaluation with the potential to replicate in similar primary care settings. To improve the evaluation’s inferential strength, we hope to compare results with affiliated, partnered, or otherwise interested clinics concurrently treating OUD while not yet adopting MOUD 2.0. Examples of clinics for comparison could include other sites of PHHS. Since these clinics have not yet fully crossed over to MOUD 2.0, they may be potential sites for intra- and multi-site stepped wedge randomized clinical trials of MOUD 2.0, pending initial results of the implementation evaluation. A stepped wedge design or other randomized clinical trial would also avoid the limitations of observational studies discussed further below (25).

Data will be de-identified prior to statistical analysis and reporting. Therefore, the Philadelphia Department of Public Health and Thomas Jefferson University IRB provided the evaluation exempt status.

### Setting and population

Given the clinic’s size and an accrual time of 2 years including before and after algorithm implementation, we anticipate approximately 100 participants for this evaluation. Participants will be individuals age 18 or older with current or past experience of homelessness and a diagnosis of OUD. All participants are patients at the ICC. Demographic information will be reported. The sample for comparing adherence will be restricted to participants already enrolled in the ICC for management of OUD prior to the algorithm implementation, measuring adherence at 6 months prior to implementation and 6 months after. Survival curves will be drawn from all aggregated patients in MOUD programs at 6 months pre-implementation to implementation or dropout, and from 6-12 months post-implementation or dropout.

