### Evaluation procedures, data sources, and variable abstraction

Evaluation procedures are limited to review of medical records that will already be in existence. The evaluation will include participants who received treatment for OUD between 6/1/2022 and 1/1/2024 and a random sample of patients without OUD within the same date range. Follow up information will be included on all participants up until 1/1/2025.

Data will be collected through retrospective chart review of the ICC’s electronic medical record. Corresponding to the listed date ranges, these data will be measured at six months before implementation of MOUD 2.0 and six months after implementation. Data will then be de-identified and sent to team members for analysis.

Demographics and medical history will have already been included in the electronic medical record from the standard intake forms used to begin patient encounters. Variables to be abstracted from the medical record include:

Demographic information: age, sex, racial self-identification.Adherence to MOUD (categorical, based on positive buprenorphine toxicology or concurrent negative opioid and buprenorphine toxicology) at collection time point.Use of opioids during treatment periods.Months in MOUD program, up to 1 year.Month/year of MOUD visits.Month/year of LAIB injection.Results of urine drug screens while in program.Treatment Effectiveness Assessment Score (21).Results of HIV/HCV screening labs while in program.Dates, dosage, and quantity of buprenorphine prescriptions.

Adherence is difficult to determine from self-report in patients with OUD due to factors like diversion, stigma, and bias (26, 27). Previously published non-LAIB algorithms did not incorporate objective measures besides self-report. To improve accuracy in treatment, adherence will be determined based on toxicology as described in the algorithm.

The approach to urine drug screening was non-standard in the months prior to implementation and continues to reflect the harm reduction approach to treatment. Therefore, adherence will be operationalized as having a minimum of 3 buprenorphine- and norbuprenorphine-positive (“appropriate”) drug screens over a 6-month period regardless of substance use. Each screen should be at least 2 weeks apart within this time period. In each phase of the evaluation, participants will be dichotomized into “adherent” vs “non-adherent” using the above definition.

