### Data analysis

Baseline and demographic characteristics will be summarized with descriptive statistics such as means and standard deviations for continuous variables such as age and percentages for categorical variables such as race.

To accommodate the need for OUD treatment centers to have fair and ethical treatment of patients at the clinic-wide level, we will use patients as their own controls and assess six-month adherence before and after program implementation. The evaluation will follow the same patients, either adherent or non-adherent at six months before algorithm implementation, by chart review to see if they crossed over to the opposite outcome six months after implementation. We will present adherence at endpoints six months prior to and six months after MOUD 2.0 implementation as proportions. We will qualitatively compare the proportion of adherence six months prior, i.e. adherence in 2022, to the proportion six months after. Then, a chi-squared test will compare discordant pairs, i.e. patients who became newly adherent after MOUD 2.0 and patients who became newly non-adherent.

Because we are treating adherence as a binary outcome, we will use McNemar’s test to determine differences in adherence before and after implementation, with each individual patient before and after implementation as a paired sample. The Chi-squared test statistic for McNemar’s test takes the form:

$$\chi^{2}=\frac{{\left(b-c\right)}^{2}}{b+c}$$

where χ^2^ follows the chi-squared distribution with 1 degree of freedom, *b* represents the patients who were adherent before and were not adherent after, and *c* represents the patients who were not adherent before and were adherent after.

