Finally, we will present unadjusted six-month survival curves for retention before and after implementation. While comparing unadjusted survival curves before and after MOUD program implementation has potential for survival bias (i.e., individuals need to “survive” to program implementation in order to be considered for post-implementation calculations), this comparison is given to provide a general sense of how MOUD 2.0 might affect the clinic overall and not to predict explicit dropout rates. If there is a significant number of patients not retained, descriptive statistics for this group will be reported to characterize factors associated with dropout. Secondary outcomes such as receipt of LAIB and use of opioids and of other substances during the evaluation periods will be analyzed with linear regression models for descriptive purposes. These primary and secondary outcomes may also be used for a future stepped wedge analysis in other clinics that could use the algorithm prospectively.

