### Evaluation status

The MOUD 2.0 clinical algorithm was developed during the COVID-19 pandemic and implemented in the ICC in January 2023. The protocol for a retrospective implementation evaluation of the algorithm was given notice of IRB exemption in February 2023. As the evaluation involves retrospective chart review, no patients were actively recruited during this time period, but new patients continue to enroll or elect to discontinue treatment, and follow up of patients for this evaluation will be completed in early 2025. This manuscript was based on protocol version 3.

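### The paired adherence test makes no allowance for time in the programme, so early exit and late enrolment can unbalance McNemar's cells without any algorithm effect, in a direction the protocol does not determine

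*Protocol article*

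**What the plan says.** Under Setting and population, the article says of the adherence comparison: "The sample for comparing adherence will be restricted to participants already enrolled in the ICC for management of OUD prior to the algorithm implementation". The same sentence then gives the timing of the two assessments as "measuring adherence at 6 months prior to implementation and 6 months after". Implementation was in January 2023.

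Under Evaluation procedures, data sources, and variable abstraction, adherence means "having a minimum of 3 buprenorphine- and norbuprenorphine-positive (“appropriate”) drug screens over a 6-month period regardless of substance use". On spacing it adds: "Each screen should be at least 2 weeks apart within this time period". In each phase "participants will be dichotomized into “adherent” vs “non-adherent” using the above definition". The required count is the same whether a patient was in the programme for one month of the window or for six.

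Under Data analysis, McNemar's statistic (b − c)²/(b + c) is referred to chi-squared with 1 degree of freedom. Cell b holds patients adherent before and not after; cell c holds the reverse. The comparison is between "patients who became newly adherent after MOUD 2.0 and patients who became newly non-adherent".

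Turnover is expected. Evaluation status notes that "new patients continue to enroll or elect to discontinue treatment". Data analysis admits survival bias, in that "individuals need to “survive” to program implementation in order to be considered for post-implementation calculations", but only for the unadjusted retention curves. The adherence test carries no such caveat.

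**The concern.** McNemar's test takes b and c to be equal in expectation when nothing has changed. Here two kinds of patient have a shortened chance to collect 3 screens, one kind in each window.

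- A patient who was adherent before and leaves early after implementation has few or no later screens. By the stated definition that patient becomes newly non-adherent and enters b.
- A patient who enrolled a few weeks before January 2023 can seldom reach 3 spaced screens before, but can do so after. That patient enters c as newly adherent.

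Neither event says anything about response to the algorithm. They cancel only if they happen to be about equally common. Adherence is the only primary outcome for which the article specifies a formal test, so an imbalance could appear as a significant fall or gain, or could hide a real gain. The article also intends to set adherence beside retention to see whether the implementation favours one over the other. That contrast blurs when early exit is itself scored as non-adherence.

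**Working it through.** The article gives no expected b, c or attrition rate for this test, so there is no figure of its own to reproduce. The sample size of 86 comes from a proportional-hazards formula with no stated inputs, and nothing below depends on it. Every rate below is an assumption.

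**1. Algebra.** Let p be the share who would be adherent in a fully observed window, s the share switching each way with no effect, d the share who leave too early to reach 3 screens after, and e the share who enrol too late to reach 3 screens before. Let d and e be unrelated to adherence and to each other. Then

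- P(b) = (1 − e)[s + (p − s)d]
- P(c) = (1 − d)[s + (p − s)e]
- P(c) − P(b) = p(e − d)

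The expected net change is zero only if e = d, and its sign follows that balance.

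**2. Numbers with exit only (e = 0).** Take N = 100, p = 0.6, s = 0.1, d = 0.2.

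- b = 100 × (0.1 + 0.5 × 0.2) = 20
- c = 100 × 0.1 × 0.8 = 8
- chi-squared = 12²/28 = 5.14, above 3.84

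Simulating the statistic gives a significant false fall in 65% of runs at d = 20%, 24% at d = 10% and 92% at d = 30%. The nominal rate in this direction is 2.5%. With p = 0.4 the rates for d = 10%, 20% and 30% are 14%, 39% and 68%.

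Not every leaver counts towards d. If leaving is uniform over 26 weeks, the share leaving before a third screen is 12/26 = 46% with 4-weekly screening and 6/26 = 23% with 2-weekly screening. So d = 10% corresponds to total attrition of about 22% (0.10/0.46) or 43% (0.10/0.23) if every screen is positive, and less if some are missed or negative.

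**3. Numbers with late entry.** Take N = 100, p = 0.5, s = 0.1.

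- d = 20%, e = 0: expected b 18, c 8; false fall 52%.
- d = 20%, e = 10%: b 16.2, c 11.2; false fall 16%.
- d = 20%, e = 20%: b 14.4, c 14.4; about 2.6% in each direction.
- d = 10%, e = 20%: b 11.2, c 16.2; false gain 16%.

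**4. Screen-level model.** Assumptions: 80 pairs; one screen a month in both windows; each patient's chance of an appropriate screen drawn from a Beta distribution with mean 0.6 and concentration 4; exponential exit times giving the stated six-month attrition; late entry as the mirror image of exit; no algorithm effect; test at 3.841.

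- No attrition, no late entry: 73% adherent in both windows, b and c both about 9.
- 20% attrition, no late entry: 73% to 63%, b about 16, c about 8; false fall about 39% (repeat runs 39% to 41%).
- 20% attrition, 10% late entry: false fall about 13%.
- 20% attrition, 20% late entry: 63% in both windows, b and c both about 13; close to nominal in each direction.
- 20% attrition, 30% late entry: false gain about 12%.

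**5. Hidden gain.** In the same model without late entry, give every patient a true gain of 15 points in the chance of an appropriate screen. Significant benefit is found in 79% of runs with no attrition, 32% at 10% attrition and about 7% at 20%.

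**The case against.** A reader might infer that attrition falls only in the after window, so the test is bound to lean towards a fall. The documents do not support that. The sample rule requires enrolment before implementation, not presence through the whole before window, so recent enrolees are admitted and feed cell c. Evaluation design describes a steady patient population, and if entry balances exit the two effects can cancel, as steps 3 and 4 show. The 39% figure belongs to the case with no late entry and should not be quoted alone.

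Screening frequency is a second reason not to fix a direction. The article calls screening before implementation non-standard, and Table 1 sets mostly two-weekly visits afterwards. How many of those visits include a screen is not stated. In the screen-level model with 20% attrition and no late entry, 4 screens before and 6 after gives a false gain in about 48% of runs.

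Third, not all exits are ordinary attrition. Table 1 contains referral and discharge outcomes that the algorithm itself produces. For a clinic-wide question, counting leavers as non-adherent is a defensible choice. This stands, and it is why the planned test should be kept.

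Finally, a rule for leavers or late enrolees may sit in the full protocol or analysis plan, so its absence from the article is not held against it. What remains rests on text the article does fix: the sample rule, the unadjusted count and the test. Dropping leavers from the pairs would restore the nominal error rate if leaving is unrelated to adherence, but it selects retained patients.

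**Conclusion.** The concern holds in a limited form. As written, the paired test can depart from b = c with no algorithm effect because the count ignores time in the programme. The expected net change is p(e − d), so both size and sign depend on exit and late-entry rates that the article does not report. In the illustrative model at 20% attrition, the result runs from a false fall in about 39% of runs, through no distortion, to a false gain in about 12%, as late entry goes from 0% to 30%. Those figures assume equal monthly screening, no link between leaving and adherence, and leavers kept in the pairs as non-adherent. The stated definition implies the last of these, but no sentence says it. The general acknowledgement of confounding in the Discussion does not cover this, because the imbalance is built in by the sample rule and the endpoint. It should be addressed before the adherence result is interpreted. It does not invalidate the evaluation.

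**What to change.** Keep the planned McNemar test in all pairs as the clinic-wide result, and add the following.

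1. Split cell b into patients who left the programme and patients still enrolled. Among leavers, separate algorithm referral or discharge from other exits where the chart shows it.
2. Split cell c into patients who enrolled during the before window and patients enrolled throughout.
3. Repeat the paired test in patients enrolled through both full windows, labelled as adherence while in treatment.
4. State that a change in adherence will not be read as response to the algorithm unless it also appears in that repeat analysis.
5. Extend the survival-bias caveat now given for the retention curves to the adherence test.

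The cost is small. Months in programme, visit months, prescription dates and screen results are already on the abstraction list. Reason for exit is not listed and would need one more look at the charts of those who left.

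The repeat analysis has fewer pairs and selects retained patients. It does not correct for unequal screening frequency, so it must be read beside the full-sample result.

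A placebo-date comparison, applying the same rule at July 2022, is optional and should not carry the conclusion. It would need charts from before the 6/1/2022 inclusion date, and its early-2022 window overlaps the pandemic-era practice that the article dates to March 2022.

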## Methods

### Study objectives

The objective of this implementation evaluation is to assess whether the MOUD 2.0 algorithm improves treatment adherence and retention in the treatment program at the clinic-wide level, compared to these outcomes before implementation. The primary outcome measures are quantified adherence to MOUD and time length of retention in the treatment program.

Adherence will be operationalized as having a minimum of 3 buprenorphine appropriate drug screens (resulting positive for buprenorphine and norbuprenorphine) over a 6-month period regardless of substance use. Retention in treatment will be measured as the proportion of participants with at least 180 days of continuous pharmacotherapy with a medication prescribed for OUD, with no gaps greater than seven days (22). These outcome measures will show whether retention rates increase along with adherence, or whether the implementation favors one outcome measure over the other. The two measures are not mutually exclusive. In the context of an implementation evaluation, adherence could theoretically be more indicative of clinical response to the algorithm, whereas retention could characterize patient buy-in of the implementation. Secondary outcomes will include the percentage of patients starting LAIB for the first time, illicit use of substances per self-report and toxicology, and results of infectious disease while in the program.

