### MOUD 2.0 algorithm

The MOUD 2.0 algorithm was implemented at the clinic-wide level in January 2023. Staff at the ICC, Pathways to Housing PA, and PHHS developed the algorithm for use at follow-up visits for OUD after the initial diagnosis visit (see **Table 1** and below **Figure 1**). The algorithm has 4-, 8-, and 12-week decision points to guide treatment for patients with varying responses to sublingual and injectable buprenorphine.

**Table 1 T1:** MOUD 2.0 status and algorithm responses.

Status	Symptoms	Opioid Use	Opioid level	BUP adherence	BUP level	Plan	Visit interval
Full response	Improved	None	Negative	Full	Appropriate	Continue current dose	2 weeks in-person alt 2 week TH option OR 4 weeks in-person
Partial response with BUP	Improved	Some	Positive	Partial	Appropriate	Consider: Increase dose Regular BH f/u LAIB	2 weeks in-person alt 2 week TH option
Partial response without BUP	Improved	Some	Positive	Partial	Negative OR Adulterated OR Late	Review dosing method Consider: Increase dose Regular BH f/u LAIB	2 weeks in-person for up to 12 weeks LAIB or refer at week 12
Minimal or nonresponse without BUP	No improvement	Some	Positive	Partial	Negative OR Adulterated OR Late	Review dosing method Consider: Increase dose Regular BH f/u LAIB	2 weeks in-person for up to 8 weeks LAIB or refer at week 8
Reconsider diagnosis of OUD	Any	Any	Negative	Any	Negative OR Adulterated OR Late	Review hx/reconsider diagnosis of OUD	2 weeks in person Discharge or refer at 4 weeks

“Appropriate” indicates buprenorphine and norbuprenorphine detected in urine without contaminants.

*BUP* buprenorphine, *BH f/u* behavioral health follow up, *LAIB* long-acting injectable buprenorphine, *OUD* opioid use disorder, *alt TH* alternating telehealth.

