### Algorithm development, staffing, and funding in a low-barrier setting

The ICC, the setting for the development of the algorithm, provides medical, behavioral health, substance use treatment, and housing services. Since 2016, the clinic’s services have included low-barrier, primary care-based MOUD. The low-barrier approach was first described with methadone maintenance therapy (29) and has been extended to buprenorphine treatment (30). This approach includes same-day treatment entry, harm reduction, flexibility in appointments and prescribing, and combining services in one location.

The ICC participates in the Pathways housing-first model, which offers immediate access to one-bedroom scattered-site apartments with intensive support services for people with experiences of chronic homelessness. All participants have a diagnosis of a serious mental illness or substance use disorder. Many participants were previously living unsheltered in the Kensington neighborhood of Philadelphia, a neighborhood often called the “epicenter of the opioid crisis,” with high levels of OUD, homelessness, food insecurity, and early mortality (31–33). The ICC continued increasing the number of people treated for OUD and modified its services throughout the COVID pandemic. As multiple other low-barrier MOUD clinics have reported, the ICC MOUD program made several intentional adjustments to MOUD care delivery to facilitate access despite disruptions. Such adjustments included: 1. extended visit intervals of up to 2 weeks during the initiation and stabilization phase of treatment with telehealth options, and, 2. a goal of monthly urine drug screening for all patients, but tolerating longer intervals without penalty.

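### The paired adherence sample sets no minimum time in the programme before implementation, so late enrollees can add to the newly adherent cell of McNemar's test but not to its opposite

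*Protocol article*

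**What the plan says.** Under Setting and population, the Protocol article defines who enters the paired comparison: "The sample for comparing adherence will be restricted to participants already enrolled in the ICC for management of OUD prior to the algorithm implementation". The sentence goes on to the timing, "measuring adherence at 6 months prior to implementation and 6 months after", but gives no length of prior enrolment. The Evaluation procedures section asks only that a participant was treated for OUD at some point between 6/1/2022 and 1/1/2024.

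Study objectives defines adherence as "having a minimum of 3 buprenorphine appropriate drug screens" over a 6-month period. Evaluation procedures adds the spacing rule, "Each screen should be at least 2 weeks apart within this time period", and says that in each phase "participants will be dichotomized into" adherent or non-adherent. There is no third, not-evaluable class, and the count of 3 is not scaled to time enrolled.

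The Data analysis section applies McNemar's test to the pairs. Cell b holds patients adherent before and not after, and cell c holds the reverse. The algorithm was "implemented at the clinic-wide level in January 2023". Before that, the clinic worked to "a goal of monthly urine drug screening for all patients, but tolerating longer intervals without penalty".

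**The concern.** A fixed count over a fixed window is a fair yardstick only if every patient could be observed for the whole window. The entry rule guarantees no such observation before implementation. A patient who joined in mid-December 2022 has two or three weeks in which to collect 3 spaced screens beforehand, and a full six months afterwards if still in care. The dichotomy records that patient as non-adherent before, although the real reason is lack of time.

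McNemar's statistic depends only on b and c. A patient who could not have been adherent before can be concordant non-adherent, which adds nothing, or fall in c. Cell b is closed to that patient. Each late enrollee who later reaches 3 screens thus counts as a success for the algorithm, even if the algorithm changed nothing. McNemar's is the only hypothesis test that the article specifies for a primary outcome. The survival-bias caveat in Data analysis concerns the retention curves, not this unequal observation time.

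**Working it through.** **The plan's own figures.** The article gives no number of late enrollees and no expected b or c, so there is nothing of the plan's to reproduce on this point. The stated 86 comes from a proportional-hazards formula without inputs and has no bearing on the paired test. I use N = 100, the anticipated size.

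**Step 1: time needed to qualify.** Three screens at least 14 days apart span at least 2 × 14 = 28 days. Enrolment under about 4 weeks before implementation makes adherence before impossible. At monthly screening, three screens take about 2 to 3 months.

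**Step 2: beyond the strict limit.** Assume monthly screens, each appropriate with probability 0.6 (an assumption). The probability of at least 3 appropriate screens is then:

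| Screens available | P(at least 3) |
|---|---|
| 2 | 0 |
| 3 | 0.6³ = 0.22 |
| 4 | 0.48 |
| 5 | 0.68 |
| 6 | 0.82 |

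The disadvantage is absolute at first, then graded.

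**Step 3: effect on McNemar's test when the algorithm does nothing.** Assumptions: adherence 50% in both windows, within-patient correlation 0.4, no loss after implementation, and a share r of the sample that cannot reach 3 screens before implementation. Among fully observed patients:

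- P(adherent both times) = 0.5² + 0.4 × 0.5 × 0.5 = 0.35
- P(each type of discordance) = 0.50 − 0.35 = 0.15

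The expected cells are b = 100(1 − r) × 0.15 and c = 100(1 − r) × 0.15 + 100r × 0.50. Rejection rates come from 40,000 simulated trials using the article's uncorrected statistic, (b − c)²/(b + c), at the two-sided 5% level:

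| r | Expected b | Expected c | Rejection |
|---|---|---|---|
| 0 | 15.0 | 15.0 | 5.4% |
| 5% | 14.25 | 16.75 | 7.2% |
| 10% | 13.5 | 18.5 | 13.7% |
| 20% | 12.0 | 22.0 | 40.1% |
| 30% | 10.5 | 25.5 | 74.0% |

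From r = 10% upward, nearly all rejections favour the algorithm. Over adherence of 40 to 70% and correlation of 0.2 to 0.6, rejection runs from 9 to 32% at r = 10% and from 24 to 83% at r = 20%.

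**Step 4: the opposite force.** Let a fraction d leave after implementation, independently of prior status, and count as non-adherent. Then b = 100(1 − r)(0.15 + 0.35d) and c = [100(1 − r) × 0.15 + 100r × 0.50](1 − d).

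- r = 0, d = 10%: b = 18.5, c = 13.5; rejection about 14%, nearly all against the algorithm.
- r = 0, d = 15%: b = 20.25, c = 12.75; rejection about 26%, again against it.
- r = 15%, d = 15%: b = 85 × 0.2025 = 17.2; c = (12.75 + 7.5) × 0.85 = 17.2. The two forces cancel.

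**The case against.** The strongest reply is that the article already implies a full pre-window. The entry sentence goes on to measurement six months either side, and Data analysis speaks of patients whose status is known six months before implementation. A December 2022 enrollee had no status then. This shows that the text can be read the narrower way. It does not make that reading a rule: no section states a minimum enrolment, and a patient with too few screens is simply classed non-adherent. Nor is this detail left to a fuller document, because the article states the entry rule itself.

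A second reply is that late enrollees may be few. Evaluation design describes a steady OUD population. The article does report that "The ICC continued increasing the number of people treated for OUD", but that sentence is about the COVID period and is no evidence on intake in late 2022. This stands: the share is unknown, and at 5% the effect is small.

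Three stronger readings are tempting, and the document does not support them.

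- *Every recent enrollee is non-adherent before by construction.* That is strict only under about 4 weeks. A November enrollee is disadvantaged but not excluded.
- *Ten or so late enrollees turn a null result significant.* With b = 8 and c = 8 + 10 = 18, the statistic is 10²/26 = 3.85 (p = 0.0499). But those ten are patients who later became adherent. At 50% adherence that takes about 20 late enrollees.
- *The test must favour the algorithm whatever it does.* Table 1 sends some patients to referral or discharge at weeks 4, 8 and 12. Anyone adherent before who leaves and is classed non-adherent enters b, and Step 4 shows that this can offset or outweigh the late-enrollee effect.

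**Conclusion.** The entry rule for the paired sample is faulty as written. It pairs a possibly truncated pre-window with a full post-window under a fixed count, and that closes cell b to the latest enrollees. Taken alone, the defect tilts the primary adherence test toward benefit. Its size rests on the late-enrollee share, which the article does not give, and on the assumed adherence, correlation and absence of later loss. It is negligible to modest at a 5% share and serious at 20%. With post-implementation loss the net direction cannot be stated. A possible cancellation does not rescue the test: two uncontrolled biases of unknown size would leave either a positive or a null result hard to interpret. The point should be settled before the data are analysed.

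**What to change.** In Setting and population, restrict the primary paired sample to patients enrolled for OUD management throughout the 6 months before the implementation date and in care on that date. Bring the inclusion sentence in Evaluation procedures and the description of the pairs in Data analysis into line with it. Report the number excluded, and show the currently worded, wider sample as a sensitivity analysis.

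State how patients who leave after implementation are classified. If they stay in the denominator as non-adherent unless they meet the rule, say that this biases against the algorithm, possibly by a material amount (Step 4), rather than calling it mildly conservative. Add a sensitivity analysis limited to patients observed through both windows. That analysis selects on staying in care, so it should be read beside the primary one and not in its place.

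The cost is a few sentences and fewer pairs. No new data are needed: months in the programme, visit month and year, and prescription dates are already on the abstraction list.
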